### Data collection, measures, management and analysis

Data collection will follow the study design and the patient flow described in figure 1.

**Figure 1 F1:**
[figure not shown]
Overview of MARES-1, 2 and 3, with participant flow and assessments. ACQ-7, Asthma Control Questionnaire; CAAT, Chronic Airway Assessment Test; COLA-6, short version of COPD in Low-income and Middle-income Countries Assessment; COPD, chronic obstructive pulmonary disease; CRDs, chronic respiratory diseases; FeNO, fractional exhaled nitric oxide; MARES, Multimorbidity Approach for REspiratory Solutions; PRISm, Preserved Ratio Impaired Spirometry; SBQ, Symptom-Based Questionnaire.

#### MARES-1

Data collection will be conducted at a single visit by a member of the UFSCar research team. All eligible participants will provide written informed consent prior to study procedures. The following procedures will be carried out:

Initial assessment (details below).Application of case-finding tools questionnaires:COLA-6 questionnaire.^19 20^Symptom-Based questionnaire (SBQ).^32^Fractional exhaled nitric oxide (FeNO) measurement.Spirometry (prebronchodilator and postbronchodilator).Application of disease-specific questionnaires:Chronic Airways Assessment Test (CAAT) for all individuals with abnormal spirometry or CRD.^33 34^Asthma Control Questionnaire (ACQ-7) for individuals with isolated or overlapping asthma.^35 36^Participants identified with abnormal spirometry results and diagnosis of CRD will be provided with an informational leaflet containing basic guidance about abnormal spirometry or asthma or COPD and how to access diagnostic and treatment services for respiratory conditions.

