### MARES-3

Participants with abnormal spirometry or diagnosis of CRD from MARES-1 and those identified as high risk for CRDs in MARES-2 will be contacted for a follow-up visit 6 months after their initial participation. Follow-up will take place at the respective BHUs/FHUs and will be conducted by the UFSCar research team in a single day. Multiple contact options will be collected at baseline, and up to three telephone attempts will be made at follow-up; participants lost to follow-up will be documented and analysed. Procedures include:

FeNO measurement.Spirometry (prebronchodilator and postbronchodilator).Application of disease-specific questionnaires:CAAT for all individuals with abnormal spirometry or CRD.^34^ACQ-7 for individuals with isolated or overlapping asthma.^36^Basic information about access to health services for diagnosis and treatment will be provided to participants with abnormal spirometry and diagnosis of CRD.Qualitative interviews with individuals selected to reflect diversity of participants (n=30) to explore their healthcare experiences, particularly regarding access to respiratory diagnosis and care.

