### Assessments

All assessments will be conducted by a team of clinical researchers who were previously trained to ensure the accuracy and consistency of data collection.

MARES-1 initial assessment: The research team will collect information about medical history, CRD risk factors, history of infections, current medications and previous hospitalisations. Additional information on childhood growth and development, socioeconomic profile and anthropometric data will be gathered.

COLA-6 questionnaire: The COLA-6 questionnaire,^19^ translated and culturally adapted into Portuguese^20^ (see online supplemental material), will be administered (MARES-1 and MARES-2). The questionnaire comprises three sections: (1) six questions addressing respiratory symptoms, functional status and exposure to risk factors; (2) one question on age and (3) one question involving peak expiratory flow (PEF) measurement. Scoring assigns 1 point for each affirmative response to the six questions, 1 point if participant is aged ≥55 years, 1 point if PEF is between 250–399 L/min, and 2 points if PEF is <250 L/min, resulting in a total score ranging from 0 to 9 points. PEF will be measured using a Mini-Wright Standard Peak Flow Meter (Clement Clarke, Essex, England). Participants will perform three forced exhalations from full lung capacity, using a nose clip, and following proper technique (avoiding neck flexion and tongue obstruction of the mouthpiece). Standardised verbal encouragement will be provided, with a 30 s pause between manoeuvres. If the two highest values differ by more than 40 L/min, up to two additional manoeuvres will be performed, to a maximum of five attempts. The highest recorded PEF value will be used.^37^ A COLA-6 score ≥4 is considered a positive test, representing the optimal combination of sensitivity and specificity for predicting the risk of COPD.^19^ Participants identified as at risk of CRDs in MARES-2 will receive their results along with educational material developed with the support from our patient and public involvement (PPI) group. The materials provide information on CRDs, risk factors, symptoms, diagnosis and treatment.

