### Data analysis

MARES-1: We will summarise the demographic and clinical characteristics of participants overall. Based on spirometry results, we will report the prevalence of COPD, asthma, PRISm and restriction, alone and in combination, with 95% CIs. For the primary analysis, we will calculate the AUC of the ROC curves for COLA-6 compared with the gold standard spirometry diagnosis separately for combined CRDs, asthma, COPD, PRISm and restriction. Using the previously published threshold for COLA-6 scores of ≥4,^19^ we will also calculate sensitivity, specificity, and negative and positive predictive values. In addition, based on the ROC curve, we will identify the COLA-6 score threshold that achieves sensitivity of at least 90%. Similar AUC analyses will be conducted for SBQ and results compared with those for COLA-6.

MARES-2: Descriptive statistics will be used to characterise the patient and healthcare professional demographics. Quantitative analysis will assess fidelity data, with categorical variables reported as frequencies (percentages). The qualitative analysis of the interviews will follow Braun and Clarke,^46^ which consists of six phases: (1) familiarisation with the data set; (2) coding; (3) generation of initial themes; (4) development and review of themes; (5) refinement, definition and naming of themes and (6) writing. The initial analysis of the transcripts obtained from the interviews will be carried out using the Web Qualitative Data Analysis software (University of Aveiro, Aveiro, Portugal) and completed manually using a Microsoft Excel spreadsheet. To ensure reliability, the criteria of credibility, transferability, dependability and confirmability will be used.^47^

MARES-3: Descriptive statistics will be used to describe the individual samples from MARES-1 and MARES-2. For patients from MARES-2, the proportions diagnosed with CRDs at spirometry will be calculated. For individuals in MARES-1, who have longitudinal data, the mean change in spirometric values from baseline to 6 months will be summarised and the proportion with improved values will be reported. Additionally, baseline and 6-month CAAT and ACQ-7 questionnaire scores, and FeNO will be summarised and mean changes reported. Estimates will be provided with 95% CIs. The qualitative analysis of the interviews will follow Braun and Clarke,^46^ as described above for MARES-2.

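### As listed, baseline FeNO in MARES-1 follows the COLA-6 peak-flow blows but 6-month FeNO in MARES-3 follows no forced manoeuvre, so the FeNO mean change compares readings taken under different conditions

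*Protocol article*

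**What the plan says.** **Baseline.** The protocol article, MARES-1 under data collection, puts everything in one session: "Data collection will be conducted at a single visit by a member of the UFSCar research team". After the initial assessment the list runs "Application of case-finding tools questionnaires:COLA-6 questionnaire.^19 20^Symptom-Based questionnaire (SBQ).^32^Fractional exhaled nitric oxide (FeNO) measurement.Spirometry (prebronchodilator and postbronchodilator", followed by CAAT and ACQ-7.

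**What COLA-6 contains.** Under Assessments, COLA-6 is more than a set of questions. Its third section is "one question involving peak expiratory flow (PEF) measurement", for which "Participants will perform three forced exhalations from full lung capacity, using a nose clip". If the two best values differ by more than 40 L/min, "up to two additional manoeuvres will be performed, to a maximum of five attempts". The same paragraph says that COLA-6 "will be administered (MARES-1 and MARES-2"; MARES-3 is not named.

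**Follow-up.** The MARES-3 list is "FeNO measurement.Spirometry (prebronchodilator and postbronchodilator).Application of disease-specific questionnaires:CAAT" and so on. It has no COLA-6 and no peak-flow-meter test.

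**Use of the readings.** Table 2 has mean change in airway inflammation, measured by FeNO, as a MARES-3 outcome. Data analysis says of the MARES-1 participants that their questionnaire scores "and FeNO will be summarised and mean changes reported", with 95% CIs. Assessments also states that participants are classified from spirometry together with FeNO.

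**The concern.** A before-after difference is interpretable only if both readings are taken in the same way. The FeNO technique is described once for both visits (device, flow, number of attempts, repeatability), and FeNO is listed ahead of spirometry at both. PEF, which sits inside COLA-6, is the one forced manoeuvre that comes ahead of FeNO, and it does so at baseline only.

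If repeated forced exhalation has any short-term effect on FeNO, that effect is in the baseline reading and not in the 6-month reading. It would have the same sign across participants, so a larger sample would not average it out. There is no comparison group in which it would show. It could be read as a change in airway inflammation, or it could hide one. Because baseline FeNO contributes to the MARES-1 classification, a shift could in principle reach that as well.

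**Working it through.** The article gives no FeNO mean, standard deviation or target change, so there is no stated figure to reproduce. The check compares the two lists and then illustrates the possible size.

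**Step 1: the sequences**

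| Step | MARES-1 baseline | MARES-3, 6 months |
|---|---|---|
| Before FeNO | Initial assessment; COLA-6 with 3 to 5 forced PEF blows; SBQ | No forced manoeuvre listed |
| FeNO | Yes | Yes, listed first |
| After FeNO | Spirometry; CAAT and ACQ-7 where applicable | Spirometry; CAAT and ACQ-7 where applicable |

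Spirometry is listed after FeNO at both visits, so it neither causes nor removes the difference. No rest interval between PEF and FeNO is stated.

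**Step 2: is the list a sequence?** Assessments states that CAAT and ACQ-7 come after FeNO and spirometry, which agrees with the list order. That is consistent with a sequential reading but does not prove it for PEF and FeNO.

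**Step 3: size of a possible artefact.** Let *m* be the true mean FeNO, with no true change over 6 months, and let *f* be the fraction by which prior PEF shifts the baseline reading. The spurious mean change is *f* × *m* in absolute size. It is a rise if baseline is lowered and a fall if baseline is raised. Both inputs are assumptions. With *m* = 30 ppb:

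- *f* = 0%: 0 ppb
- *f* = 5%: 0.05 × 30 = 1.5 ppb
- *f* = 10%: 0.10 × 30 = 3.0 ppb
- *f* = 15%: 0.15 × 30 = 4.5 ppb

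**Step 4: comparison with the precision of the estimate.** The article expects 309 MARES-1 participants to enter follow-up (146 + 77 + 86 = 309), before losses. The 95% CI half-width is 1.96 × SD / √309. The SD of change is assumed to be 10 to 25 ppb:

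- SD 10: 1.96 × 10 / 17.58 = 1.1 ppb
- SD 25: 1.96 × 25 / 17.58 = 2.8 ppb

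At a mean of 30 ppb, a shift would equal the half-width at *f* = 1.1/30, about 4%, if the SD is 10, and at *f* = 2.8/30, about 9%, if the SD is 25. Within the assumed range the artefact may therefore be nothing, or may exceed the reported precision. The documents cannot say which.

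**The case against.** The strongest reply has five parts.

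- **The order is inferred.** The MARES-1 procedures are an unnumbered list, and the article refers to Figure 1 for the patient flow, which is not available here. That CAAT and ACQ-7 come last is forced anyway, since eligibility for them depends on the test results. This stands as a limit on certainty. The list is still the only order that the text gives.
- **Operational detail may lie elsewhere.** FeNO is to follow American Thoracic Society guidelines, and a rest interval could be in a full protocol or operating procedure. The SBQ also falls between PEF and FeNO. This stands in part: the interval is unknown, not shown to be short. A rest at baseline would reduce the difference, but the two visits would still not match.
- **No effect is documented.** Nothing in the article says that forced exhalation alters FeNO, or in which direction. This stands. A reader might infer that the 6-month change is biased in every participant, or biased in a known direction; the text supports only a difference in conditions.
- **Two comparisons fail.** A 10% shift at 25 ppb is 2.5 ppb, which matches the repeatability limit in the FeNO paragraph. That limit is a quality rule for readings within 15 minutes, not a threshold for meaningful change over 6 months. A reader might also infer that participants cross the 25 and 50 ppb bands; Figure 2, which shows how FeNO enters the classification, is not available, so this cannot be checked.
- **The obvious reordering has a cost.** Placing FeNO ahead of the whole of COLA-6 would let the assessor see a component of the reference classification before asking the index questions and coaching an effort-dependent PEF. That could compromise the main MARES-1 accuracy analysis. This stands, and it shapes the remedy.

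The stakes are also modest. The stated aim of MARES-3 is access to services, and FeNO change is one of several descriptive summaries with no test or decision attached.

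**Conclusion.** The point holds as a difference in measurement conditions, not as a demonstrated bias. Followed as listed, the plan takes FeNO after three to five forced exhalations at baseline and after none at 6 months, then reports the within-person mean change without a control group. Under an assumed shift of 0 to 15% at an assumed mean of 30 ppb, the artefact is 0 to 4.5 ppb; the range includes zero and the direction is unknown. The baseline classification that uses FeNO may be touched, but this cannot be confirmed from what is shown. The MARES-1 sample size is not affected.

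Severity is minor. Confidence is moderate on the order of procedures, because it is read from a list, and low on the size of any effect.

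**What to change.** In the MARES-1 visit, split the COLA-6 administration and state the order explicitly:

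1. Initial assessment.
2. COLA-6 questions, then SBQ.
3. FeNO, with the reading withheld from the assessor until PEF is recorded.
4. COLA-6 PEF measurement.
5. Spirometry, then CAAT and ACQ-7 where applicable.

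FeNO then precedes every forced manoeuvre at both visits, the index questions still precede any component of the reference classification, and the MARES-3 visit needs no change.

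Flag participants already measured with PEF before FeNO and report their FeNO change separately from those measured in the new order.

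The cost is a small change to the visit worksheet, a COLA-6 given in two parts, and a simple arrangement for withholding the FeNO value. No extra visit or device is needed.

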#### MARES-2

This study comprises three phases.

##### Phase 1: Implementation of COLA-6

Application of COLA-6 questionnaire: After receiving prior training from the UFSCar research team, healthcare professionals at the BHUs and FHUs will identify potentially eligible individuals with NCDs who attend PHC services and will administer the COLA-6 questionnaire as part of their routine care. Participants identified as high risk for CRDs based on COLA-6 results will be provided with an informational leaflet containing basic guidance about pulmonary health and how to access diagnostic and treatment services for respiratory conditions.

Fidelity monitoring: The research team at the UFSCar will observe the administration of the COLA-6 at the beginning and end of all applications by each healthcare professional to ensure adherence to the protocol.

##### Phase 2: Participant enrolment and assessment

Following the administration of the COLA-6 as part of routine care, healthcare professionals will inform individuals who meet the inclusion criteria about the research and invite them to participate. Individuals expressing interest will be referred to the research team, who will subsequently contact them to provide detailed study information and obtain written informed consent. On consent, the research team will conduct the initial assessment (details below).

##### Phase 3: Evaluation of implementation

On completion of the 50 COLA-6 applications, healthcare professionals will participate in qualitative interviews conducted by the UFSCar team to explore the barriers and facilitators to implementation in routine PHC settings.

### MARES-3

Participants with abnormal spirometry or diagnosis of CRD from MARES-1 and those identified as high risk for CRDs in MARES-2 will be contacted for a follow-up visit 6 months after their initial participation. Follow-up will take place at the respective BHUs/FHUs and will be conducted by the UFSCar research team in a single day. Multiple contact options will be collected at baseline, and up to three telephone attempts will be made at follow-up; participants lost to follow-up will be documented and analysed. Procedures include:

FeNO measurement.Spirometry (prebronchodilator and postbronchodilator).Application of disease-specific questionnaires:CAAT for all individuals with abnormal spirometry or CRD.^34^ACQ-7 for individuals with isolated or overlapping asthma.^36^Basic information about access to health services for diagnosis and treatment will be provided to participants with abnormal spirometry and diagnosis of CRD.Qualitative interviews with individuals selected to reflect diversity of participants (n=30) to explore their healthcare experiences, particularly regarding access to respiratory diagnosis and care.

### Assessments

All assessments will be conducted by a team of clinical researchers who were previously trained to ensure the accuracy and consistency of data collection.

MARES-1 initial assessment: The research team will collect information about medical history, CRD risk factors, history of infections, current medications and previous hospitalisations. Additional information on childhood growth and development, socioeconomic profile and anthropometric data will be gathered.

COLA-6 questionnaire: The COLA-6 questionnaire,^19^ translated and culturally adapted into Portuguese^20^ (see online supplemental material), will be administered (MARES-1 and MARES-2). The questionnaire comprises three sections: (1) six questions addressing respiratory symptoms, functional status and exposure to risk factors; (2) one question on age and (3) one question involving peak expiratory flow (PEF) measurement. Scoring assigns 1 point for each affirmative response to the six questions, 1 point if participant is aged ≥55 years, 1 point if PEF is between 250–399 L/min, and 2 points if PEF is <250 L/min, resulting in a total score ranging from 0 to 9 points. PEF will be measured using a Mini-Wright Standard Peak Flow Meter (Clement Clarke, Essex, England). Participants will perform three forced exhalations from full lung capacity, using a nose clip, and following proper technique (avoiding neck flexion and tongue obstruction of the mouthpiece). Standardised verbal encouragement will be provided, with a 30 s pause between manoeuvres. If the two highest values differ by more than 40 L/min, up to two additional manoeuvres will be performed, to a maximum of five attempts. The highest recorded PEF value will be used.^37^ A COLA-6 score ≥4 is considered a positive test, representing the optimal combination of sensitivity and specificity for predicting the risk of COPD.^19^ Participants identified as at risk of CRDs in MARES-2 will receive their results along with educational material developed with the support from our patient and public involvement (PPI) group. The materials provide information on CRDs, risk factors, symptoms, diagnosis and treatment.

SBQ: The SBQ questionnaire^32^ will be administered to compare performance with COLA-6 (MARES-1). The SBQ consists of 11 questions covering age, smoking history, body mass index, cough, wheezing, allergies, dyspnoea, exposure to dust or chemical particles and the presence of respiratory diseases during childhood. A total score of ≥17 indicates a higher risk for COPD.^32^

FeNO measurement: FeNO will be measured using a portable analyser (FeNObreathe, Geratherm Medical Latin America, Brazil), following American Thoracic Society guidelines^38^ to assess type 2 airway inflammation (MARES-1 and MARES-3). Subjects will be seated comfortably and instructed to inhale through the mouthpiece for 2–3 s to total lung capacity, followed by a steady exhalation lasting at least 6 s, without air leakage. An expiratory flow rate of 50 mL/s will be maintained, monitored by a sound signal. Up to six manoeuvres will be allowed, with 30 s intervals between attempts. The highest value among three acceptable measurements will be used, ensuring quality control by limiting deviation to ≤2.5 ppb or 10% within 15 min. FeNO levels will be classified as low/normal (<25 ppb), intermediate (25–50 ppb) or high (>50 ppb).^39^

Spirometry: Lung function will be assessed using a portable spirometer (Spirobank II Advanced, MIR, USA) to confirm or exclude CRDs (MARES-1 and MARES-3). Testing will follow American Thoracic Society and European Respiratory Society standards, ensuring A or B quality grades. ^40 41^At least three forced, acceptable and reproducible manoeuvres will be performed before and 20 min after inhalation of 400 mcg of salbutamol sulfate. Spirometry results will be reviewed and interpreted by a board-certified pulmonologist.

Participants will be classified based on spirometry and FeNO results (figure 2) into two groups, primarily according to the recommendations of the Global Initiative for Chronic Obstructive Lung Disease^42^ and the Global Initiative for Asthma.^27^

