### Statistical methods

#### Sample size

MARES-1: The sample size calculation was based on the performance of the COLA-6 questionnaire for diagnosing COPD in the GECo study (sensitivity: 45.7%; specificity: 86.5%) and assuming a COPD prevalence of 17% in Brazil.^45^ With these assumed values, a minimum sample size of N=859 individuals will allow us to estimate the area under the ROC curve (AUC) to within 4.5% (based on a 95% CI). According to prevalence studies for CRDs in Brazil, we calculate that we will identify approximately 146 individuals with COPD, 77 with asthma and 86 with Preserved Ratio Impaired Spirometry (PRISm) or restriction in this study, giving an estimated sample of 309 with abnormal spirometry and 550 with normal spirometry. We will case-find in more people if the expected prevalence is lower to reach these targets.

MARES-2: The number of BHU/FHU that will be involved in this study, as well as the number of health professionals (N=20) responsible for applying the COLA-6 questionnaire, was a pragmatic decision. Based on the GECo study,^19^ of the total individuals evaluated (N=1000), we anticipate that 16.4% (N=164) will be identified as at high risk for CRDs (COLA-6≥4) and 836 will be identified as at low risk for CRDs. We will case-find in more people if the expected prevalence is lower to reach these targets.

MARES-3: The sample size expected (N=473) is dependent on samples obtained from MARES-1 and MARES-2. Considering the prevalence found in the GECo study^19^ and prevalence available for the Brazilian population, we estimate that we will have up to 218 individuals with COPD, 100 with asthma and 100 with PRISm.

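### FeNO is taken as the highest of three flow-controlled readings, which biases it slightly upward against fixed cut-offs; the mean of the same readings is less biased and less noisy

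*Protocol article*

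**What the plan says.** Under Assessments, the FeNO paragraph fixes the expiratory flow at 50 mL/s and sets the number of attempts: "Up to six manoeuvres will be allowed, with 30 s intervals between attempts". It then gives the summary rule, "The highest value among three acceptable measurements will be used", followed by the agreement requirement, "ensuring quality control by limiting deviation to ≤2.5 ppb or 10% within 15 min". Whether that requirement limits the range of the three readings or each reading's distance from their mean is not stated.

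The single value is then categorised: "FeNO levels will be classified as low/normal (<25 ppb), intermediate (25–50 ppb) or high (>50 ppb"). It also enters the diagnostic grouping: "Participants will be classified based on spirometry and FeNO results (figure 2) into two groups". Under Data analysis, MARES-3 uses FeNO as a change measure: "Additionally, baseline and 6-month CAAT and ACQ-7 questionnaire scores, and FeNO will be summarised and mean changes reported".

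The article gives no reason for choosing the maximum and plans no mean-based version.

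**The concern.** The same section takes the highest peak expiratory flow, which is natural for a measure limited by effort. FeNO is measured differently. Flow is held constant, and readings count only if they agree within a narrow limit, so differences among accepted readings are mostly repeat-measurement variation. The largest of three such readings is a biased estimate of the person's level and wastes information that the other two carry.

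With fixed cut-offs, a small upward shift moves some people just under a boundary into the next category. FeNO is part of the classification against which COLA-6 is judged, so a one-directional shift in it is worth removing if that costs nothing. In MARES-3 the issue is extra within-session variance in the change score.

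**Working it through.** The article states no figure for FeNO bias or misclassification, so there is none to reproduce.

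**Inputs from the article:** maximum of three acceptable readings; limit of 2.5 ppb or 10%; cut-offs <25, 25–50 and >50 ppb; MARES-1 sample size 859.

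**Assumed, because the article does not give them:** log-normal FeNO with median 15–25 ppb and geometric SD 1.8–2.1; within-session SD (σ) equal to the larger of 0.5–1.5 ppb and 2–6% of the value.

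**Step 1, bias and variance.** For three independent normal repeats, before any limit on spread:
- E[max] − E[mean] = 3/(2√π) σ = 0.846σ
- Var(max) ≈ 0.56σ²; Var(mean) = σ²/3 ≈ 0.33σ²

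**Step 2, the cap.** If the range is at most r, then max − mean ≤ 2r/3 (reached when the two lower readings are equal).
- At 25 ppb, r = 2.5 ppb, so the cap is 2 × 2.5/3 ≈ 1.7 ppb.
- At 50 ppb, r = 5 ppb, so the cap is 2 × 5/3 ≈ 3.3 ppb.
- If the limit instead means distance from the mean, the caps are 2.5 and 5 ppb.

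**Step 3, crossings.** Triplets were simulated over the assumed ranges. Only those with range within the larger of 2.5 ppb and 10% were kept, with and without rounding to whole ppb.

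| Quantity | Maximum compared with mean |
|---|---|
| Average shift | about 0.5–1.2 ppb |
| Share ≥25 ppb | about +0.7 to +3.0 points, or 6–26 of 859 |
| Share >50 ppb | about +0.1 to +1.1 points, or 1–9 of 859 |

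In a central scenario (median 20, geometric SD 1.8, σ the larger of 1 ppb and 4%, unrounded), the share ≥25 ppb goes from 35.2% to 37.0% (about 15 people). The share >50 ppb goes from 6.0% to 6.6% (about 5 people). Rounding to whole ppb changes these to about 23 and 3.

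**Step 4, hand check of that scenario.** Crossings ≈ 859 × density at the cut-off × average excess there.
- At 25 ppb: z = ln(25/20)/ln 1.8 = 0.380, and density = φ(0.380)/(25 × 0.588) = 0.0253 per ppb. The untruncated excess of 0.846 ppb gives 859 × 0.0253 × 0.846 ≈ 18. The limit trims the excess to about 0.69 ppb, which gives about 15.
- At 50 ppb: z = 1.559 and density = 0.00403 per ppb. With σ = 2 ppb the untruncated excess of 1.69 ppb gives about 5.9. Trimmed to 1.38 ppb, it gives about 4.8.

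Both trimmed figures agree with the simulation.

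**Step 5, MARES-3.** With the same rule and similar variability at both visits, the expected excess is the same at each and drops out of the mean change. The within-session part of the variance of one person's change is 2 × 0.56σ² = 1.12σ² with the maximum and 2 × 0.33σ² ≈ 0.67σ² with the mean. With σ = 1 ppb and all 309 expected MARES-1 participants returning, that part contributes √(1.12/309) ≈ 0.06 ppb or √(0.67/309) ≈ 0.05 ppb to the standard error. The gain is real but small.

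**The case against.** The rule is explicit, reproducible, applied alike to everyone and bounded by a repeatability limit. The primary analysis is the AUC of COLA-6, which FeNO can affect only through the classification in Figure 2. The FeNO distribution and within-session SD are assumptions. The article follows a cited measurement guideline and cited cut-offs, and if those cut-offs were built on a maximum or a single reading, the mean is not automatically the matching summary. All of this stands, and it limits the size of the point. It does not remove the bias and variance argument.

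Several stronger readings are tempting but unsupported:

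- **That every value is pushed up.** Tied readings do not move; with whole-ppb output, about 5–25% of accepted triplets would be ties.
- **That errors go only one way.** This holds against the sample mean. Against the person's true level, all three readings fall below it one time in eight (½³), and then the maximum is also too low.
- **That the shift is routinely 5%.** That requires every triplet to span the full 10%. With a geometric SD of up to 2.2 it would give up to 28 crossings at 25 ppb and 15 at 50 ppb, which is a worst case.
- **That these are mostly added high-FeNO results.** Most crossings are at 25 ppb, from low/normal to intermediate.
- **That the crossings can be set against the 77 expected asthma cases.** The forecast "we will identify approximately 146 individuals with COPD, 77 with asthma and 86 with Preserved Ratio Impaired Spirometry (PRISm) or restriction" rests on prevalence studies, not on a FeNO rule. Without Figure 2 it is not known which cut-off counts or whether FeNO acts alone.
- **That MARES-3 mean change is biased.** The shift largely cancels there.

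**Conclusion.** The concern holds as a minor, easily corrected choice of summary statistic. The highest of three accepted readings overstates their mean by about 0.85 within-session SD for unrestricted normal repeats, and by less once the repeatability limit is applied: about 0.5–1.2 ppb on average under the stated assumptions. That corresponds to roughly 6–26 of 859 participants moving to 25 ppb or above and 1–9 moving above 50 ppb. The direction follows from order statistics alone; the counts depend on the assumed distribution and repeatability. The documents do not support any stated number of altered asthma or chronic respiratory disease labels, nor a claim that the COLA-6 AUC is materially affected.

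**What to change.** Replace the rule with the mean of the three acceptable readings, at both MARES-1 and MARES-3, and report results based on the highest value as a sensitivity analysis. Before fixing this, confirm which summary (mean, single reading or maximum) the cited 25 and 50 ppb cut-offs were based on, and state it. In the same edit, say whether the 2.5 ppb or 10% limit applies to the range or to distance from the mean.

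The cost is one sentence and one derived field, with no additional manoeuvres. If recruitment has begun, the value must be recomputed for those already measured, which is possible only if all three readings were recorded. The case report form should therefore hold each one.
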